Mentalization-based treatment (MBT, [13]) has specifically been developed for the treatment of individuals with BPD. MBT is an integrative psychodynamic treatment rooted in attachment theory [14]. It assumes that mentalizing vulnerabilities lie at the core of the disorder. Mentalizing is the imaginative ability to interpret and understand the behaviour of oneself and of others in terms of mental states and develops in early attachment relationships [15]. Empirical research has shown that mentalizing is highly impaired in individuals with BPD especially with regard to emotionally intense relationships [14]. MBT follows distinct therapy rationales and is assumed to help alleviate BPD symptoms through inter alia improving mentalizing and epistemic trust, i.e. the trust in interpersonally transmitted information being relevant, trustworthy and generalizable for the individual [16]. MBT, alongside dialectical behaviour therapy (DBT; [17]), is the most studied psychotherapy for BPD. Five randomized-controlled trials (RCTs) have investigated the efficacy of MBT in BPD in comparison to psychiatric services [18], structured clinical services including supportive psychotherapy [19, 20], specialist BFT [21] and in adolescents with non-suicidal self-injury (NSSI) who mainly fulfilled criteria for BPD [22]. MBT proved to be superior to bona fide treatment (BFT)/clinical management in NSSI, suicide attempts, psychiatric symptoms, and hospitalization [18, 22] as well as core BPD symptoms [22, 23]. One RCT found MBT as effective as a specialist treatment-as-usual (TAU) for the primary outcome, reduction of Borderline symptom severity, with large effect sizes for both groups; however, there were significantly fewer drop-outs in the MBT group [21]. One independent RCT confirmed positive effects for MBT in comparison to supportive therapy for general functioning and BPD symptoms, suggesting that MBT may address core problems in BPD beyond NSSI and suicidality [20]. MBT is the only treatment for which superiority to clinical management was demonstrated in all primary outcome variables as well as a significantly higher level of employment or academic/occupation training eight years after randomization [24]. Findings also demonstrate that MBT shows superiority over TAU for interpersonal problems and general functioning [25]. In sum, MBT has demonstrated reliable improvements for psychiatric symptoms.

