### Primary outcome

#### Crisis events – composite outcome

The primary outcome of the study is the incidence of crisis events as indicated by 1) suicides, 2) suicide attempts, or 3) self-harm behavior.

To assess suicide attempts and self-harm behavior, the following four questions taken from the Self-Harm Behaviour Questionnaire ([53], German version: [54]) will be used: “Have you ever intentionally hurt yourself or caused yourself pain? (e.g. scratched with fingernails or with other sharp objects?)”, “How often have you intentionally hurt or caused yourself pain?”, “Have you ever tried to take your own life?” and “How often did you try to take your own life?”. These questions will be adapted for the Ecological Momentary Assessment (e.g., “Since the last signal have you ever intentionally hurt or caused yourself pain? (e.g., scratched with fingernails or with other sharp objects?”). Only if any of the crisis events occurred, the patient will be asked to indicate the frequency of the event(s).

Crisis events like suicides cannot be reported by the patient themselves but should be taken into account as well (see e.g. Bateman and Fonagy [18]). Suicides are recorded via the Serious Adverse Events (SAE) reports.

To increase ecological validity, the incidence of crisis events 1) – 4) will be assessed during one week each month over the course of 12 months of treatment, and one week every three months post treatment up to the 12-month-follow up (T3). During the assessment week, patients will be asked to complete one online-assessment every other day, resulting in 4 assessments per assessment week.

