### Primary analysis

The purpose of this trial is to show whether the (incidence) rate of crisis events (suicides, suicide attempts, self-harm behavior recorded throughout therapy and up to 12 month after therapy) is lower for BPD-patients undergoing MBT than for BPD-patients undergoing a BFT. The null-hypothesis (H01) to be tested can be formulated as follows: The (incidence) rates of crisis events in the MBT and in the BFT group are the same. A log-linear (Poisson) regression model (GLMM) will be used to fit with treatment group, sex and age as explanatory variables, along with log of observation (treatment + follow-up) time as an offset. The randomization cluster will be considered as random effect. Poisson regression lends itself to analysis of count data, considering that more events of suicidal behavior within a time frame are worse than one, and controlling for the period of observation by using it as an offset in the model. The null hypothesis (H01) of no treatment effect will be tested using Wald type tests on the regression coefficient of the treatment group (MBT vs. BFT). Tests will be two-sided at the 0.05 level.

Missing values will be replaced using multiple imputation using fully conditional specification methods (FCS) considering randomization cluster, sex, age and the respective value over time.

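### The primary model's offset is time in the trial, but non-fatal crisis events are counted only in EMA weeks, so the rate ratio is biased if EMA dropout timing or prompt response differs by arm

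*Protocol article*

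**What the plan says.** **Offset.** Under Primary analysis, the Protocol article specifies a log-linear mixed model for the number of crisis events, with treatment, sex and age as covariates, randomization cluster as random effect, "along with log of observation (treatment + follow-up) time as an offset". The stated purpose is "controlling for the period of observation by using it as an offset in the model".

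**Counting of events.** Under Crisis events – composite outcome, incidence "will be assessed during one week each month over the course of 12 months of treatment", and then in one week per quarter up to the 12-month follow-up. Prompts come every other day, "resulting in 4 assessments per assessment week". Suicides come instead from serious adverse event (SAE) reports.

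**Missing data.** Under Compliance/rate of loss to follow-up, the Poisson model is said to cope with unequal numbers of measurements per person. Under Primary analysis, missing values are also to be multiply imputed by fully conditional specification. Neither section says what offset an imputed patient receives.

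**Retention.** The article expects 30% drop-out during therapy. The Background cites a trial in which "there were significantly fewer drop-outs in the MBT group", and Aim, design and setting lists therapy retention among the outcomes on which MBT is expected to be superior.

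**The concern.** An offset turns a count into a rate only if it measures the time during which an event could be counted. Here the numerator accrues in EMA weeks and the denominator in months of treatment plus follow-up. The two are not proportional across patients, because assessed weeks per month fall threefold at month 12. Early leavers contribute only the densely sampled year, so their apparent rate is too high. A missed prompt that is not imputed acts in the opposite direction: it adds offset time without a chance to record an event.

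If leaving or non-response differs between arms, part of the estimated rate ratio reflects retention instead of crisis events. If MBT patients stay in EMA longer, the dropout component favours MBT, which is the trial's hypothesis. This model carries the trial's primary hypothesis test.

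**Working it through.** The article gives no exposure figure to reproduce. Its power figure can be reproduced and is not in dispute. With 152 patients per arm, the effective number is 152 × 0.7² / (1 + 7 × 0.1) = 43.8. With means of 5 and 3.75, SE² = (1/5 + 1/3.75)/43.8, which gives 79.6% power at two-sided 0.05, against 78% stated from simulation.

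**Inputs from the article:** 12 EMA weeks in year 1, 4 in year 2, 24 months of observation, target rate ratio 0.75, expected therapy drop-out 30%. **Assumptions:** the split of EMA dropout by arm, the month of leaving, and a constant event rate per EMA week.

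**Step 1. Assessed weeks for a patient leaving at month t.** cov(t) = t for t ≤ 12, and 12 + (t − 12)/3 afterwards. A completer has 12 + 4 = 16 weeks, or 112 of 730 days (15.3%).

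**Step 2. Apparent rate relative to a completer,** [cov(t)/t] / (16/24):

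| Leaves at month | EMA weeks | Weeks per offset month | Ratio to completer |
|---|---|---|---|
| 12 or earlier | t | 1.00 | 1.50 |
| 15 | 13 | 0.87 | 1.30 |
| 18 | 14 | 0.78 | 1.17 |
| 24 | 16 | 0.67 | 1.00 |

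**Step 3. Apparent rate ratio when the true ratio is 1.** For an arm with dropout proportion d at month t, the apparent rate is [(1 − d) × 16 + d × cov(t)] / [(1 − d) × 24 + d × t].

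| Dropout MBT / BFT | Month | MBT | BFT | Apparent ratio |
|---|---|---|---|---|
| 30% / 30% | 6 or 12 | equal | equal | 1.00 |
| 25% / 35% | 6 | 13.5/19.5 | 12.5/17.7 | 0.98 |
| 25% / 35% | 12 | 15/21 | 14.6/19.8 | 0.97 |
| 20% / 40% | 6 | 14/20.4 | 12/16.8 | 0.96 |
| 20% / 40% | 12 | 15.2/21.6 | 14.4/19.2 | 0.94 |

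The first three splits all average the expected 30%. A true ratio of 0.75 would appear as 0.72 or 0.70 in the last two rows.

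**Step 4. Effect of the remedy.** In a Poisson simulation (1,500 runs, 152 per arm, no cluster effect, dropout in months 1 to 12 of 20% against 40%, true ratio 1), the time-in-trial offset gave a ratio of 0.957 and rejected in 14.1% of runs. An offset of EMA time covered gave 0.999 and 5.4%. With 30% in both arms, both offsets were unbiased. The rejection rates are only indicative, since clustering is left out.

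**Step 5. Interaction with imputation.** For a patient leaving at month 12, the rate relative to the truth under each pairing is:

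| Count | Offset | Relative rate |
|---|---|---|
| Observed (12 weeks) | Observed, 12 months | (12/12)/(16/24) = 1.5 |
| Imputed to 16 weeks | Observed, 12 months | (16/12)/(16/24) = 2.0 |
| Observed (12 weeks) | Full, 24 months | (12/24)/(16/24) = 0.75 |
| Imputed to 16 weeks | Full, 24 months | (16/24)/(16/24) = 1.0 |

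Only the last pairing is coherent, and its offset is then the same for everyone. The article does not say which pairing it intends.

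**The case against.** **Observation time may mean observed EMA time, and the analysis plan may say so.** The article does refer all analyses to a statistical analysis plan. But it also fixes the offset, and its parenthesis defines observation time as treatment plus follow-up. Nothing links it to answered prompts or EMA weeks. The wording needs correcting wherever the detail ends up.

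**Therapy dropout is not EMA dropout.** This stands. The 30%, the cited trial and the retention hypothesis all concern leaving treatment, and the article intends to analyse all 304 patients. A difference between arms in EMA follow-up is plausible, not established, and its size is unknown.

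**The sampling change is harmless in itself.** This also stands. With equal dropout and response, the drop in density at month 12 does not bias a constant rate ratio.

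Three stronger readings are tempting and not supported:

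- A reader might infer a ratio as low as 0.82 to 0.89 (20% against 40%). That needs counts imputed to the full schedule over time truncated at dropout, a pairing that the article leaves open but does not state.
- A reader might infer 0.875 or 1.14 from unequal prompt response. Those figures assume 70% against 80% response, which the article does not give, and no imputation of missed prompts, although it says missing values will be imputed.
- The example item "Since the last signal have you ever intentionally hurt or caused yourself pain" might suggest that the first prompt of a week reaches back to the previous EMA week, adding a further distortion. If it did, the prompts would jointly span the whole calendar period and the density problem would largely disappear, so the two claims exclude each other. The article says incidence is assessed during the week and gives this item only as an example. The look-back is therefore not counted here as a second bias.

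**Conclusion.** The offset as written does not match how non-fatal events are ascertained. At a constant event rate, it gives a patient who leaves by month 12 an apparent rate 1.5 times that of a completer. That patient-level distortion follows directly from the schedule.

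Bias in the treatment comparison is conditional on EMA dropout timing or prompt response differing by arm. Under the assumed dropout splits, a true null becomes about 0.97 to 0.98 (25% against 35%) or 0.94 to 0.96 (20% against 40%). This is a spurious reduction of roughly 2% to 6%, against a targeted 25%. It is modest, but it favours MBT if MBT retains more patients in EMA, and it is avoidable. The two missing-data devices are unreconciled; pairing full imputed counts with truncated time would enlarge the bias.

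**What to change.** Choose one of two coherent specifications and state it before analysis:

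1. **Preferred.** Define the offset as the log of EMA time actually covered (answered prompts or days), preferably with counts and exposure by period and a year-1/year-2 term.
2. **Alternative.** Impute per EMA window to the full schedule, and use the full scheduled EMA time as the offset for every patient.

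State explicitly that imputed full counts are not combined with truncated time. Also state that only events within the EMA week's fixed recall window are counted. In the separate analysis of suicides, which are recorded continuously through SAE reports, keep calendar time as the denominator.

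The cost is a change of wording plus some extra work to derive each patient's exposure. The article does not describe how prompt-level data are stored, so the team should confirm that answered prompts can be identified.

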To investigate efficacy of MBT versus BFT, a total of *n* = 544 patients with a BPD diagnosis will be screened for eligibility at five study sites in Germany: University Hospital Heidelberg (Institute for Psychosocial Prevention, ST, and Department of General Psychiatry, SHe), University Hospital Jena (Institute for Psychosocial Medicine, Psychotherapy and Psychooncology, BS), University Hospital Düsseldorf (Clinic for Psychosomatic Medicine and Psychotherapy, UDE & JR), University Hospital Ulm (Clinic for Psychosomatic Medicine and Psychotherapy, HG, JV), Psychologische Hochschule Berlin (Department of Clinical Psychology and Psychotherapy, TS). Of the patients screened, *n* = 304 are expected to fulfil all inclusion criteria including informed consent to participate in the trial, to complete the baseline assessment (T0) and to be allocated to the trial (Fig. 1). Patients will be randomized in groups of 8 (randomization cluster) in a 1:1 ratio to either MBT or BFT using block randomization. Randomization will be stratified by study site. For randomization, study site coordinators will use a centralized web-based tool (randomizer.at) to maintain allocation concealment. Role-based user rights ensure that only approved study personnel may perform randomizations. Main assessments will be conducted for both arms at 6 months (in-therapy assessment, T1), at 12 months (T2) and at 24 months after start of therapy (12-months follow-up, T3). A final sample of *n* = 304 is expected to be obtained for data clearance and analysis using an intent-to-treat protocol. A drop-out of 30% during therapy is expected and acknowledged in our power analysis. Blinding of study team, trial personnel at site as well as patients is not feasible due to the nature of the interventions. Only central assessors will be blind to treatment. Allegiance bias is minimized as the consortium includes representatives of all trial treatments (MBT, group therapy, BFT).

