**Table 1 Tab1:**
[figure not shown]
*S*chedule of enrolment, interventions, and assessments

^a^EMA: every second day, one week per month in the first year and one week every three months in the second year

^b^after each therapy session and at t_1_ and t_2_

Data will be gathered and managed via redcap by the data coordinator (SHa) of the PI’s (ST) study site. Clinical monitoring will be conducted by the independent clinical monitor KKS to ensure patient safety, protocol adherence, and data consistency. For important protocol modifications, approval of the ethics committee will be obtained and the protocol published on the clinicaltrials.gov website will be updated.

Treatment duration in BFT is delivered as usual (according to the German Psychotherapy-Guidelines “Richtlinienpsychotherapie”). Thus, it can be shorter or longer than MBT (12 to 100 h); however, the average number of BFT treatment is comparable with 48 sessions per patient [48]. The length of BFT will not be controlled for by the study to ensure BFT conditions as in the German routine health care. Exact treatment length and dose will be assessed. To avoid the effects of attention bias, supervision will be regularly offered to therapists in both arms in their respective methods in a group setting. All interventions are implemented as face-to-face interventions. Individual and group therapists can be the same or different therapists. All therapies in the trial will be paid for by the German health insurances.

All therapy sessions will be video-recorded or, if video is not possible, audio-taped. Ten percent of random sample recordings from early and late phases of therapy across the whole recruitment phase will be analysed by external coders for therapist adherence. Trial results will be communicated by publication in journal articles and by congress participation.

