### Power calculations and sample size

In an RCT of MBT vs. structured clinical management (SCM), Bateman and Fonagy [19] encountered a mean count of 1.8 cases of critical behaviour in MBT vs. 2.6 cases in the SCM group at 12 months of treatment, resulting in a relative risk of 0.7. In another randomized controlled study of MBT vs. standard psychiatric care [18], the median count of self-mutilation in a 6-months period was reduced from 9 to 1 in MBT and from 8 to 6 in standard psychiatric care. As we expect our comparator to be more effective than the comparators used in the previous studies, we are raising the relative risk in order not to overestimate the effect of MBT. Accordingly, we assume 10 events per patient in the control group and 7.5 cases in the MBT group for the whole 24-months period, and would rate a relative risk of 0.75 [112] as sufficiently relevant requiring a model setting as described below to successfully reject the null hypothesis of no effect. As a more conservative approach, we assume less events (but the same relative risk), i.e. 5 events in the control group per patient and 3.75 in the treatment group. Therefore, a log-linear model (Poisson regression) with treatment as explanatory variable, and number of crisis events in 24 months as response, with a mean of 5 events expected for the BFT and 3.75 for the MBT group, results in a relative risk of 0.75. A test of the null hypothesis “no association between treatment and primary endpoint” at α = 0.05 level rejected with a power of 78% if 8 patients could be enrolled per cluster and 38 clusters could be randomized simulated with R assuming a dropout rate of r = 30% and an intraclass-correlation coefficient of 0.1 (ICC). The dropout rate is taken into account using the correction factor of 1/(1-r)^2 according to [113]. The sample size was corrected with help of the ICC according to [114].

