### Compliance/rate of loss to follow-up

Building on similar trials comparing MBT with BFT for BPD patients we expect a compliance rate of about 70%, with Bateman and colleagues [19] achieving 99/134 = 73% compliance over 18 months and Jorgensen and colleagues achieving 63/85 = 74% compliance over 24 months [20]. Both Poisson regression for analyzing the primary outcome and multilevel models for analyzing the secondary outcomes handle unbalanced data with different number of measurements per person [115]. As such, the intent-to-treat sample is used in all analyses instead of complete cases.

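### The stated imputation model leaves out therapy drop-out, while the sample size implies that drop-outs lose the effect; the intention-to-treat rate ratio can therefore be biased

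*Protocol article*

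**What the plan says.** All references are to the protocol article; the statistical analysis plan is not shown.

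- **Primary analysis.** Missing values are replaced by "multiple imputation using fully conditional specification methods (FCS) considering randomization cluster, sex, age and the respective value over time". The section Secondary analyses gives essentially the same list twice, once for the linear mixed models and once for the ordinal model of the DASS-21.
- **Aim, design and setting.** "A drop-out of 30% during therapy is expected and acknowledged in our power analysis". Patients are randomized in groups of 8, so each cluster belongs to one arm.
- **Compliance/rate of loss to follow-up.** "the intent-to-treat sample is used in all analyses instead of complete cases".
- **Power calculations and sample size.** "The dropout rate is taken into account using the correction factor of 1/(1-r)^2". The planning rates are stated "with a mean of 5 events expected for the BFT and 3.75 for the MBT group, results in a relative risk of 0.75", and the null hypothesis is "rejected with a power of 78% if 8 patients could be enrolled per cluster and 38 clusters could be randomized".
- **Participants.** Patients with an inpatient stay of more than 4 weeks leave the study and count as drop-outs.
- **Procedure, text after Table 1.** "Exact treatment length and dose will be assessed".

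**The concern.** An intention-to-treat comparison asks what assignment to MBT rather than BFT does to the crisis rate, whether or not therapy is completed. If counts after drop-out are missing, the imputation model decides what is assumed about them. The listed model has no term that separates patients who stopped from patients who stayed. It therefore continues a drop-out's own earlier course, informed by same-arm patients of whom most are still in therapy or have completed it. In effect the on-therapy rate is carried forward.

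The sample size points the other way. If 30% of the data were simply lost, the inflation would be 1/(1-r). The squared form is the inflation for a treatment effect shrunk by (1-r), with drop-outs still analysed but showing no difference between arms. The plan thus powers the trial for drop-outs who lose the effect and then imputes them as if they kept it. What is at stake is the size of the single confirmatory rate ratio, and whether it means what its label says.

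**Working it through.** **1. Which assumption the 78% contains.** Inputs from the power and primary analysis sections: 38 × 8 = 304 patients, rates 5 and 3.75, r = 0.3, ICC 0.1, two-sided 0.05. The design effect is 1 + 7 × 0.1 = 1.7. For n effective patients per arm, SE = √(1/(5n) + 1/(λn)), where λ is the MBT rate, and power = Φ(|ln RR|/SE − 1.96).

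| Treatment of drop-out | n per arm | RR | Power |
|---|---|---|---|
| Squared factor: 304 × 0.49 / 1.7 / 2 | 43.8 | 0.75 | 79.6% |
| All 304 kept, effect diluted to 0.7 × 0.75 + 0.3 × 1 | 89.4 | 0.825 | 78.1% |
| Simple data loss: 304 × 0.7 / 1.7 / 2 | 62.6 | 0.75 | 91.5% |
| No drop-out | 89.4 | 0.75 | 97.8% |

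Only the first two rows come within 2 points of the stated 78%, and they are two ways of writing the same idea.

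**2. What the imputation does under that idea.** The schedule gives 12 EMA weeks in year 1 and 4 in year 2, 16 in all. Assumptions that are not in the article:

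- events are spread evenly over these weeks;
- all drop-outs stop at month 6 (6 of 16 weeks observed) and then give no EMA data;
- drop-outs in both arms run at the BFT rate after stopping;
- the cluster term carries the arm in full.

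True MBT mean = 0.7 × 3.75 + 0.3 × (3.75 × 6/16 + 5 × 10/16) = 2.625 + 1.359 = 3.984, so the true ratio is 3.984/5 = 0.797 (log −0.227). Imputed at the on-therapy rate, the ratio is 3.75/5 = 0.75 (log −0.288). The log effect is overstated by a factor 0.288/0.227 = 1.27. The gap of 0.061 is 21% of the assumed log effect. Drop-out at month 3 gives 27% and at month 9 gives 15%.

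A simulation with drop-out spread over year 1, between-patient variation and imputation from each patient's own history by arm gave a true ratio of 0.795 and an imputed ratio of 0.751.

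**3. How the size depends on who keeps answering.** Let m be the share of drop-outs with missing counts, with drop-out at the start of therapy. The imputed ratio is (0.7 × 0.75 + 0.3(1−m)) / (0.7 + 0.3(1−m)): 0.825 (the true value) for m = 0, 0.794 for m = 0.5 and 0.75 for m = 1. In the year-1 simulation with half missing, the imputed ratio was 0.776 against 0.795 true.

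**4. If drop-outs never benefited, even before stopping.** With month-6 drop-out and pure Poisson counts, the true ratio is 0.825. The imputed MBT mean is 0.7 × 3.75 + 0.3 × (5 × 6/16 + 3.75 × 10/16) = 3.891, ratio 0.778, a bias of 20% of the assumed log effect. With strong between-patient spread (gamma shape 0.5 to 2, assumed) it falls to 5–12%, because the patient's own earlier counts then carry information.

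**5. Whether the direction is fixed.** Assume 20% drop-out in MBT and 40% in BFT. With 8 events after drop-out in either arm, the true ratio is (0.8 × 3.75 + 0.2 × 8)/(0.6 × 5 + 0.4 × 8) = 4.6/6.2 = 0.742 against 0.75 imputed, so the benefit is slightly understated. With 10 events it is 5/7 = 0.714. With 5 events it is 4/5 = 0.80, and the benefit is overstated again.

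**The case against.** **Stopping therapy is not stopping EMA.** Assessments are planned to month 24 in both arms and 304 patients are expected in the analysis. Missing later counts follow directly from the text only for patients removed after a long inpatient stay. This stands, and it governs the size of the bias.

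**The direction is not fixed.** A reader might infer that the planned analysis necessarily favours MBT. The document does not support that. Its Background reports fewer drop-outs under MBT in one earlier trial, and step 5 shows how unequal drop-out with worse later outcomes can reverse the sign.

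**The offset may do the work.** The model has log observation time as an offset, so a lost patient could simply contribute less time, with imputation limited to missed assessments within it. This does not remove the problem: the rate seen before drop-out is then extrapolated by the model instead of by the imputation.

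**A planning factor does not define the estimand.** The article nowhere says in words that drop-outs lose the effect. That follows from the form of the factor and from the reproduced power. Conservative planning followed by a missing-at-random analysis is common. The mismatch is a reason to look at the imputation model, not proof of error by itself.

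**The test itself.** A reader might infer a false-positive risk. With equal drop-out and equal rates after stopping, no MBT effect gives a ratio of 1 both in truth and after imputation. The issue shown is the size of an existing effect.

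**The analysis plan may say more.** The variable list may not be exhaustive, and sensitivity analyses are often left to that plan. No finding is made about a missing sensitivity analysis. The list itself, however, is stated for the primary analysis and repeated for the secondary outcomes.

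**Conclusion.** The point holds as a risk of bias in the confirmatory estimate. The stated imputation model cannot distinguish drop-outs from stayers, and the sample size implies that they differ. Under equal 30% drop-out, an effect lost after stopping at month 6 and all drop-outs lost to EMA, the benefit is overstated: 0.75 imputed against about 0.80 true, or 27% on the log scale. The bias is smaller if a good share keep reporting, zero if all do, and can reverse under the unequal drop-out of step 5. The share lost to EMA, the timing of drop-out and the rates afterwards are assumptions; the article gives none of them. The concern deserves a change of wording before analysis. It does not show that the trial's test is invalid or that its result must favour MBT.

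**What to change.** In Primary analysis, and in both imputation statements of Secondary analyses, add two variables to the imputation model:

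- **Treatment arm**, so that the arm does not depend on how the cluster term is fitted.
- **Time-varying therapy status**, by EMA week for the primary outcome and by assessment time point for the others. Use two states: in therapy or regularly completed, versus prematurely terminated. BFT includes regular short-term therapy and its length is not controlled, so a short course that ended as intended must not count as drop-out.

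Missing counts after premature termination are then informed by same-arm patients who also stopped but kept reporting. With 0.3 × 152 ≈ 46 drop-outs expected per arm, these may be few, in which case the status term should be pooled over time.

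The cost is protocol or analysis-plan wording and some programming, since treatment length is already recorded. Confidence intervals will be somewhat wider. A reference-based sensitivity analysis, with missing weeks of MBT drop-outs imputed at the BFT rate to match the sample-size assumption, is optional and may already be in the analysis plan.

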### Secondary analyses

The primary analysis will be repeated for 1) suicides, 2) suicide attempts, and 3) self-harm behavior. Number of events and person-time will be tabulated against timepoint and treatment arm.

Further key secondary endpoints are the EQ- 5D- 5L, the WHODAS 2.0 Short, DASS- 21 and the BSL- 23.

The EQ- 5D- 5L, BSL- 23 and the WHODAS 2.0 Short will be analyzed by time point using a linear mixed model with baseline value, treatment group, sex and age as explanatory variables. The randomization cluster will be considered as random effect. Missing values will be replaced using multiple imputation using FCS considering randomization cluster, sex, age and the respective value over time.

The DASS- 21 will be categorized. Ordinal regression will be used for analyses using the baseline category, sex, age, and treatment group as explanatory variables. Analyses will take place by time point. The randomization cluster will be considered as random effect. Missing values will be replaced using multiple imputation using FCS considering randomization cluster, sex, age and the value over time.

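### The stated imputation lists omit treatment group; if cluster enters the imputation as a random effect, the treatment effect can be attenuated towards the null

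*Protocol article*

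**What the plan says.** Under Primary analysis, the Poisson mixed model "will be used to fit with treatment group, sex and age as explanatory variables, along with log of observation (treatment + follow-up) time as an offset", with randomization cluster as a random effect. The null hypothesis is tested on the treatment coefficient. Missing values are handled by multiple imputation with fully conditional specification, "considering randomization cluster, sex, age and the respective value over time".

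Under Secondary analyses, the models for EQ-5D-5L, BSL-23 and WHODAS also contain treatment group, with cluster as a random effect. The imputation sentence reads: "Missing values will be replaced using multiple imputation using FCS considering randomization cluster, sex, age and the respective value over time". For the DASS-21, an ordinal model containing treatment group, it reads: "Missing values will be replaced using multiple imputation using FCS considering randomization cluster, sex, age and the value over time".

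So sex, age and cluster pass from the analysis models into the imputation lists, and treatment group does not. The article does not say whether cluster is fixed or random in the imputation.

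The section on aim, design and setting states that patients are randomized in groups of eight, 1:1, so each cluster lies wholly in one arm. It also says: "A drop-out of 30% during therapy is expected and acknowledged in our power analysis".

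**The concern.** An imputation model should contain every variable of the analysis model, above all the one whose effect is tested. If it does not, imputed values are drawn as though that variable had no effect of its own, and the estimated effect moves towards zero. In a superiority trial that expects 30% drop-out, part of a null result could then come from the imputation rather than the treatments.

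The listed cluster partly protects against this because it is nested in arm. How far depends on a choice the article leaves open. The only role it ever gives cluster is a random effect, and it says so for the analysis models alone.

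**Working it through.** **1. Inputs.** From Power calculations and sample size: 38 clusters of 8 (304 patients), ICC 0.1, drop-out r = 0.30, means 5 and 3.75 (rate ratio 0.75), stated power 78%. From Primary analysis: two-sided 0.05. Not in the article, so assumed: a Gaussian outcome with unit variance, arm difference d of 0.2-0.5 SD in the formula and 0.4 SD in the simulation, correlation 0.5 between visits, ICC 0.02-0.2, and 30% of final values missing.

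**2. The plan's own figure.** Effective patients per arm = 304 × 0.7² / (1 + 7 × 0.1) / 2 = 43.8. SE of the log rate ratio = √((1/5 + 1/3.75)/43.8) = 0.103. Power = Φ(0.2877/0.103 − 1.96) = 79.6%, within two points of the stated 78%.

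**3. Shrinkage formula.** With no arm term and clusters split equally between arms, the imputation model sees a between-cluster variance of ICC + d²/4. About 8 × 0.7 = 5.6 patients per cluster are observed. The weight given to a cluster's own mean is

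λ = (ICC + d²/4) / (ICC + d²/4 + (1 − ICC)/5.6).

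Observed patients (70%) carry the full difference and imputed patients (30%) carry λ times it, so the share kept is 0.7 + 0.3λ.

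- ICC 0.1, d = 0.2: λ = 0.11/(0.11 + 0.161) = 0.406, kept 82%.
- ICC 0.1, d = 0.5: λ = 0.1625/(0.1625 + 0.161) = 0.503, kept 85%.
- ICC 0.05, d = 0.2: λ = 0.261, kept 78%.
- ICC 0.2, d = 0.5: λ = 0.648, kept 89%.
- Fixed cluster effects: λ = 1, kept 100%.
- Neither cluster nor arm: λ = 0, kept 70%.

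**4. Simulation.** 400 trials per setting, with an earlier visit in the imputation model and a true final effect of 0.4 SD. Entries are the percentage of the true effect kept. MCAR means missing completely at random; MAR means missingness depends on the earlier value.

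| Setting (effect at earlier visit) | Arm + random cluster | Fixed cluster, no arm | Random cluster, no arm | Neither |
|---|---|---|---|---|
| MCAR, ICC 0.1 (0.2) | 99 | 99 | 82 | 79 |
| MCAR, ICC 0.1 (0.4) | 98 | 97 | 87 | 86 |
| MCAR, ICC 0.1 (0) | 98 | 98 | 76 | 70 |
| MAR, ICC 0.1 (0.2) | 100 | 100 | 82 | 78 |
| MCAR, ICC 0.02 (0.2), rerun | 98 | 98 | 79 | 77 |
| MCAR, ICC 0.2 (0.2) | 99 | 100 | 83 | 79 |

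Monte Carlo error is about 2 percentage points (0.006-0.009 on 0.4). In the first ICC 0.02 run the fixed-cluster fit failed numerically in the matrix inversion, so the table shows the rerun with a tolerance. The other columns of that first run gave 102% with arm and 83% with random cluster and no arm.

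A separate set of 800 trials per setting (ICC 0.02 and 0.1) agreed. Random cluster without arm kept 78-83% with only a baseline value and 85-86% with an earlier visit. Adding arm kept 99%, and so did fixed cluster terms.

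**5. Why this is not carried to the primary test.** The 0.7² in step 2 is the plan's own drop-out correction. Without it, effective n per arm is 304/1.7/2 = 89.4 and SE = 0.0722. Diluting the log rate ratio to 70% then gives 0.7 × 0.2877/0.0722 = 2.79, the same as 0.2877/0.103 = 2.79. The planned power thus already allows for an apparent rate ratio of exp(0.7 × ln 0.75) = 0.82. Adding the imputation loss to that SE would charge the same drop-out twice.

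**The case against.** The strongest case on the other side is that arm information is not left out. All three lists contain the randomization cluster, which determines arm, and they name it beside sex and age. Entering it as a classification covariate is a natural reading, and on that reading nothing material is lost. The article also defers all analyses to a statistical analysis plan, which is not shown and may already name treatment group or settle the form of cluster. This stands, and it makes the attenuation conditional. It does not remove the point, because the article does not simply leave the matter open. It fixes a variable list, and a plan that follows that list while treating cluster as random would inherit the gap.

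A reader might infer that the primary and all key secondary results are biased. The documents do not support that. The primary count has a log-time offset, so a dropout's observed weeks can contribute directly, and the article does not say what is imputed. Neither the count nor the ordinal DASS-21 was simulated. A reader might also infer a definite loss of power for the primary test. That fails because the planned power already contains the drop-out correction.

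Nor can fixed cluster terms be dismissed as unworkable. With about 5.6 observed patients per cluster they could be unstable for ordinal or sparse outcomes, but this was not tested, and they kept the effect for a Gaussian outcome. Finally, the article's 30% is drop-out during therapy. Reading it as 30% missing endpoint values is an assumption.

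**Conclusion.** The point holds in conditional form. Treatment group is missing from all three stated imputation lists, and whether that matters depends on how cluster enters. With fixed cluster effects the loss is negligible (97-100% of the effect kept). With a random cluster effect and no arm term, about 76-87% is kept, a loss of 13-24% towards the null. With arm added, 98-102% is kept.

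These figures rest on a Gaussian outcome, 30% missing final values and the assumed effects and correlations above. They apply most securely to EQ-5D-5L, BSL-23 and WHODAS. For the primary count and the DASS-21 the size is not established. The article does not show that a bias will occur, but it leaves room for an avoidable one.

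**What to change.** Add treatment group to the imputation variables in all three sentences (one under Primary analysis, two under Secondary analyses), or impute separately within each arm. Keep randomization cluster in the imputation model and state whether it is fixed or random. With fixed cluster terms an arm term is redundant, because clusters are nested in arm; with a random cluster effect it is needed. If the statistical analysis plan already says this, it is enough to align the article's wording with it.

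The change should be made before the data are analysed. It costs a few words, needs no patients or extra data, and in the simulations restored essentially the whole effect with cluster kept random.
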